### Stratified care model for sciatica

#### Stratification algorithm

We devised an algorithm to identify those sciatica patients likely to need a fast-track referral from primary care to specialist spinal services, and those who are likely to do well with treatments available in primary care. This algorithm was based on data analysis from the ATLAS study cohort [20] which provided information on the characteristics of sciatica patients most likely to be referred to spinal specialist services. Full details of the development of the stratification algorithm will be provided in a separate paper. Here we give very brief details on the stratification algorithm and the three derived subgroups. We utilised prognostic information, using the STarT Back tool [25], and clinical information based on the following clinical examination findings: interference with ability to work (including work around the house), pain below the knee, intense leg pain, and sensory changes in the painful leg during neurological examination (loss of or reduced pin prick sensation in a dermatomal distribution in the painful leg). The algorithm allocates patients to one of three subgroups, and each subgroup is matched with a care pathway. We allocated patients to **subgroup 1**, which involves referral to primary care for management options of low treatment intensity, if their total score on the STarT Back tool was less than or equal to 3 out of a possible 9. We used a combination of the STarT Back tool score and a number of findings from the clinical examination described above to direct referral to primary care management options of higher treatment intensity (**subgroup 2**), or to fast-track patients to a specialist spinal opinion and imaging tests (**subgroup 3**). The details of the care pathways for each of the three subgroups, are presented in full later in the text, under the section ‘Stratified care arm: Matched care pathways and their delivery’.

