### Randomisation and allocation concealment

Eligible patients who consent to take part are randomised to one of the two trial arms using a 1:1 web-based randomisation service through Keele Clinical Trials Unit (CTU), ensuring allocation concealment. The clinic administrator uses the web-based randomisation method (with a back-up process to telephone the CTU for randomisation in the event of web access failure), providing details of the centre (Staffordshire, North Shropshire/Wales, Cheshire) and patient subgroup allocation. Individual patients are randomised, stratified by centre and subgroup allocation, using random permuted blocks of varying size, to either stratified care or non**-**stratified care. The administrator informs the physiotherapist of the patient’s allocation (stratified care arm or control arm) and delivery of treatment will commence within the same SCOPiC clinic visit. The patient’s GP is informed in writing that the patient is participating in the trial but are not informed about which arm of the trial the patient has been randomised to. Usual clinician to clinician correspondence continues as per normal practice and the research does not interfere with this.

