## Qualitative study

The aim of the linked qualitative study is to understand the acceptability of the ‘fast-track’ pathway in the stratified care arm of the trial, to patients and clinicians. Qualitative research on patients’ experiences of sciatica and its management is scarce [46, 47], especially in those with most severe symptoms, and qualitative studies that report clinicians’ views of managing this condition are even less common [48]. In the SCOPiC trial stratified care arm the ‘fast-track’ pathway to spinal specialist assessment and opinion is novel, and the focus of the qualitative study is on patients in this subgroup and the clinicians involved in their management.

A purposive sample of patients randomised to the stratified care arm and who are on the ‘fast-track’ pathway will be invited for interview based on treatment centre and patient demographics including age, gender, baseline leg pain severity/disability, and also response to treatment. Interviews will be conducted after the 4 month follow-up point.

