### Clinical outcomes analysis

#### Primary analysis

The primary analysis will compare time to self-reported resolution between stratified care and non-stratified care, on an intention-to-treat basis. A Kaplan-Meier survival analysis will estimate the time from randomisation until first resolution of symptoms. Participants who drop out of the trial through active withdrawal will be censored at the time this occurs (by contrast, participants not responding at any time point will continue to be followed-up until they actively withdraw). This will provide the data for comparing the relative mean and median survival times of the two trial arms. A Cox proportional hazards regression analysis will compare time to resolution between arms by calculation of a hazard ratio (HR) of rates of resolution adjusted for centre, patient stratification group (subgroups: 1, 2, 3) and baseline pain duration. The HR will be presented along with a 95% confidence interval for the HR; a p-value < 0.05 (two-tailed) based on the Wald test statistic will signify rejection of the null hypothesis of no difference in recovery time between the two arms. A statistically significant p-value with HR > 1 would indicate statistically significant shorter time to recovery for stratified care compared to control; a statistically significant p-value with HR < 1 would indicate a (statistical) significantly longer time to recovery for stratified care compared to control. The analysis will account for physiotherapist effect (proportional Cox hazards frailty model).

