#### Secondary outcomes analysis

The analysis will provide between-arm differences in secondary outcomes at 4 and 12 months and provide point and 95% interval estimates from longitudinal linear and logistic mixed effect regression models as appropriate to the outcome data being analysed adjusting for centre, stratification subgroup (1, 2, 3) (stratifying variables) and baseline pain duration. Descriptive summary of mean scores for the two trial arms and difference in mean scores (numerical outcomes) and frequency counts (percentages) along with odds ratios (categorical outcomes) will be presented, with between-arm comparisons being presented in the form of point and 95% interval estimates, alongside p-values for the test of statistical association.

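### Adding each outcome's own baseline to the secondary models, and baseline leg pain and disability to the primary Cox model, would gain efficiency at little cost; the planned analysis is valid without them

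*Protocol article*

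**What the plan says.** Under Primary analysis, the protocol article states that the HR will be "adjusted for centre, patient stratification group (subgroups: 1, 2, 3) and baseline pain duration", with a frailty term for physiotherapist. Under Secondary outcomes analysis, between-arm differences at 4 and 12 months come from linear or logistic mixed models, "adjusting for centre, stratification subgroup (1, 2, 3) (stratifying variables) and baseline pain duration". The exploratory subgroup analyses use the same three covariates.

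Randomisation is "stratified by centre and subgroup allocation, using random permuted blocks of varying size". The models therefore contain both stratifying factors, and pain duration is the one prognostic variable added to them.

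The article indicates that baseline severity data exist:

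- Recruitment procedures describes a baseline questionnaire completed before the clinic visit.
- Health economic outcomes lists EQ-5D-5L at baseline.
- Qualitative study samples interviewees on characteristics "including age, gender, baseline leg pain severity/disability, and also response to treatment".

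The content of Table 1 is not shown, so the exact baseline instruments are inferred.

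Subgroup itself carries some severity. Under Stratification algorithm it is built from the STarT Back score and from clinical findings that include "interference with ability to work (including work around the house), pain below the knee, intense leg pain", together with sensory changes.

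**The concern.** Subgroup has only three levels. Subgroup 1 is any STarT Back score of 3 or less out of 9, and the other two combine the score with clinical findings. Patients in one subgroup can still differ in leg pain and disability scores. If those scores predict outcome beyond subgroup and duration, leaving them out has two distinct effects.

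- **Linear secondary models:** variation that the baseline value could explain stays in the residual, so intervals are wider than they need be. This matters most for physical disability at 12 months, which the Sample size section calls a key secondary outcome and powers separately.
- **Cox model:** the HR is non-collapsible, so leaving out a prognostic variable pulls the estimated HR towards 1 and costs power. The most conservative primary scenario has only 80% power, so a few points would count there.

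**Working it through.** **1. The plan's own figures.** Inputs from Sample size: 470 patients (235 per arm), 20% dropout, two-sided 5%, cluster-size coefficient of variation 0.65. Evaluable: 470 × 0.8 = 376, or 188 per arm.

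- *HR 1.4, 90% power, all recovered.* Schoenfeld: 4(1.960 + 1.282)² / (ln 1.4)² = 372 events; 372 / 0.8 = 465. Freedman: (1.960 + 1.282)² × (2.4 / 0.4)² = 379 events; 379 / 0.8 = 474. Both are close to 470.
- *HR 1.5, 80% power, 60-65% recovered, ICC 0.01.* 376 × 0.60 to 0.65 = 226 to 244 events, giving power 0.861-0.887 before clustering. The design effect is 1 + ((1 + 0.65²)m − 1) × 0.01. The mean cluster size m is not stated; an assumed m of about 12-20 gives roughly 80% power at 470.
- *Disability, standardised difference 0.35.* With 188 per arm and the same design effect, power is 0.923 at m = 1 and 0.852 at m = 20. This agrees with the stated figure of more than 80%.

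None of these figures relies on a gain from covariate adjustment.

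**2. Secondary outcomes, linear models.** With within-subgroup baseline-outcome correlation r, residual variance is multiplied by 1 − r². Assumed r, since the article gives none:

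- r = 0.4: 1 − 0.16 = 0.84, so 16% lower variance; interval width × √0.84 = 0.92.
- r = 0.6: 1 − 0.36 = 0.64, so 36% lower variance; interval width × √0.64 = 0.80.

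If 0.4-0.6 is instead the raw correlation, subgroup already explains part of it and the reduction is smaller. The calculation does not carry over to the logistic models. The odds ratio is also non-collapsible, so the gain there is in power, as in the Cox model.

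**3. Primary outcome, by simulation.** Setting: 376 patients, 1:1, exponential times, 1,500 trials per row. Assumed: subgroup shares 35/40/25%, subgroup log HR −0.4 per step, duration log HR −0.2 per SD, and one residual severity index with log HR of size b per SD, independent of the rest. Centre and physiotherapist frailty were not simulated. The planned model (arm, subgroup, duration) is compared with the same model plus severity.

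| Events, true conditional HR | b | HR, planned / added | SE of log HR, planned / added | Power, planned / added |
|---|---|---|---|---|
| 62.5%, 1.5 | 0 | 1.500 / 1.501 | 0.1327 / 0.1329 | 0.863 / 0.863 |
| 62.5%, 1.5 | 0.2 | 1.487 / 1.498 | 0.1325 / 0.1329 | 0.852 / 0.861 |
| 62.5%, 1.5 | 0.4 | 1.467 / 1.511 | 0.1325 / 0.1330 | 0.834 / 0.877 |
| 62.5%, 1.5 | 0.6 | 1.427 / 1.503 | 0.1323 / 0.1331 | 0.770 / 0.859 |
| 90%, 1.4 | 0 | 1.404 / 1.405 | 0.1105 / 0.1107 | 0.873 / 0.870 |
| 90%, 1.4 | 0.2 | 1.394 / 1.409 | 0.1104 / 0.1108 | 0.858 / 0.868 |
| 90%, 1.4 | 0.4 | 1.361 / 1.408 | 0.1102 / 0.1107 | 0.807 / 0.875 |
| 90%, 1.4 | 0.6 | 1.329 / 1.414 | 0.1101 / 0.1109 | 0.723 / 0.869 |

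The standard error never falls when severity is added. Power rises because the HR is less attenuated: about 0-1 points at b of 0-0.2, 4-7 points at 0.4, and 9-15 points at 0.6. The Monte Carlo error of each power figure is about √(0.86 × 0.14 / 1,500) = 0.9 points.

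**The case against.** The adjustment set is prespecified, contains both randomisation factors and a prognostic variable, and is used consistently. Randomisation protects validity, and the test and interval already allow for chance imbalance. All of this stands.

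A reader might infer that the primary model ignores severity. It does not: intense leg pain, interference with work and the STarT Back score all enter through subgroup, so only within-subgroup information is left out. Nor does the outcome's anchoring to the patient's own baseline state show that starting severity is a strong predictor, since high severity could mean more room to improve or a worse prognosis. The 9-15 point loss needs b = 0.6, and nothing in the article supports a value that large.

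The power comparison also treats 1.4-1.5 as an HR conditional on severity. The Sample size section derives it from an 11% absolute difference between arms, which is a marginal contrast. If the design HR is closer to marginal, the stated power does not fall short, and the added covariates would be a bonus above it.

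On the secondary models, baseline may already enter as a repeated measure, and a condensed article can leave that to the analysis plan. This stands as a condition on the fix. The section itself names only 4 and 12 months and lists covariates without the baseline value. Some outcomes, such as global perceived change and satisfaction with care, have no baseline value to add.

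**Conclusion.** The point holds as an efficiency improvement of modest weight. The planned analyses are valid, and a reader who infers bias or an inadequate sample from the short covariate list goes beyond the article. So does one who infers that the HR's interval is wider than it need be: the standard error of the log HR does not shrink with the added covariates.

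The secondary-outcome part is the stronger. For continuous outcomes, residual variance would fall by up to 16-36% at an assumed within-subgroup correlation of 0.4-0.6, and by less if that range describes the raw correlation. For the primary outcome the gain is in power only: about 0-1 points for a residual log HR of 0-0.2 per SD, and 4-7 points at 0.4 per SD. Both ranges rest on assumed prognostic strength, because the article gives no figure for either. They also rest on baseline leg pain and disability having been measured as scores, as the Qualitative study section suggests.

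**What to change.** - **Secondary outcomes analysis:** add the baseline value of the outcome to each linear or logistic mixed model wherever one was measured (for example disability, leg and back pain, EQ-5D-5L). If baseline already enters as a repeated measure, say so instead. Leave outcomes without a baseline value on the current three covariates.
- **Primary analysis:** before unblinding, prespecify continuous baseline leg pain intensity and baseline disability as additional Cox covariates. Describe the aim as limiting attenuation and gaining power, not as narrowing the interval.

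The cost is small. No new data collection appears to be needed. A simple rule is required for missing baseline values. The primary HR becomes conditional on slightly more covariates, which the report should state. The sample size needs no change.

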#### Sensitivity analyses (of the primary endpoint)

The following sensitivity analyses will be carried out to test the rigour and robustness of the primary outcome evaluation through evaluation of:alternative assumptions regarding missing data – for the primary evaluation, missing data are assumed to be synonymous with non-recovery. The primary evaluation is based on ‘recovery’ at the first point of a positive response, but if any missing data immediately precede this response then all these observations are assumed to be indicative of ‘non-recovery’ – an additional sensitivity analysis will set the time interval of recovery as the mean time between the participant’s last response (indicating ‘non-resolution’) and the time at which ‘resolution’ is first classified. A more extreme sensitivity analysis will take the contrary view on missingness to equate to, and imputed as, a ‘resolved’ case.alternative assumption regarding interval censoring – to account for the fact that only the interval of time within which the resolution occurred is known, and not the exact time (especially after the first 16 weeks when outcome data is collected monthly). A further sensitivity analysis will use methods that allow for interval censoring.secondary definitions of good outcome - we will use three separate secondary classifications based on ‘stable resolution’, defined as: two consecutive recordings of ‘completely recovered’ or ‘much better’; ‘improvement’, defined as: completely recovered’, ‘much better’ or ‘better’, through single response, and ‘stable improvement’, defined as: ‘completely recovered’, ‘much better’ or ‘better’, through two consecutive responses.analysis of participants in the stratified care arm that: (i) have complete follow-up – i.e. not including censoring, and (ii) receive the treatment pathway that is correctly matched to their subgroup – as per treatment protocol.

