## Outcome measures and data collection

### Primary outcome

The primary outcome measure is time to first resolution of symptoms of sciatica, measured on a 6-point ordered categorical scale: ‘completely recovered’, ‘much better’, ‘better’, ‘same/ no change’, ‘worse’ and ‘much worse’ – the anchor being against the patients’ baseline symptoms when they attended the SCOPiC sciatica clinic (“compared to how you were at the SCOPiC clinic X weeks/months ago, how are your back and leg symptoms today?”). Patient-reported resolution of symptoms is defined as a response of either ‘completely recovered’ or ‘much better’, collected using regular text messages (or brief phone calls where text messaging is not possible). Data collection for the primary outcome occurs weekly, starting on the first Sunday following the participant’s assessment at the SCOPiC sciatica clinic, for the first 4 months for all participants. Then between 4 and 12-month follow-up, the text message data collection changes to once every 4 weeks, or until ‘stable resolution’ of symptoms, which is defined as 2 consecutive months’ responses of ‘completely recovered’ or ‘much better’. After stable resolution, data collection for the primary outcome via text message ceases. 94% of UK adults have a mobile phone (https://www.ofcom.org.uk./facts) and previous research has shown that weekly text messages are a useful method of data collection to examine the clinical course of back pain in primary care, with high mean response rate of 83% [30]. Participants who do not respond to their first week’s text message receive a reminder message 48 h later, and those who still do not respond are mailed a postcard the next day. Participants who do not respond to the second week’s text message receive a reminder message 48 h later, and those who still do not respond receive a phone call from a research nurse after at least a further 24 h. For subsequent non-response the reminder processes described is repeated. If the participant continues not to provide a response using text message there is an option to transfer to data collection by brief phone call.

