**Table 1 Tab1:**
[figure not shown]
Overview of enrolment, interventions, and assessments

*The interventions and their delivery are described in detail in the manuscript. Treatments are tailored to the individual participant and likely to have different frequency and duration for each participant. Overall, treatment for most participant is expected to be completed within 4 months from randomization

^**a**^ The trial’s primary outcome is time to symptoms resolution. Data collection with text messages for the primary outcome occurs weekly for the first 4 months for all participants. Between 4 and 12-month follow-up, the text message data collection changes to once every 4 weeks, or until ‘stable resolution’ of symptoms, which is defined as 2 consecutive months’ responses of ‘completely recovered’ or ‘much better’. After stable resolution, data collection for the primary outcome via text message ceases

^**b**^ At 4 and 12 months follow-up, data collection is via postal questionnaires

^**c**^ Participants and clinicians are asked to report any adverse and/or serious adverse events. Patients are asked about adverse events in the follow-up questionnaires

^**d**^ Global perceived change is collected via text messages or telephone calls, and in the follow-up questionnaires at 4 and 12 months

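### 'Stable resolution' has two non-equivalent definitions, and the analysis version requires 1 week of persistence before week 16 but 4 weeks after it

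*Protocol article*

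**What the plan says.** All references are to the protocol article.

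- **Primary outcome** section: texting between months 4 and 12 may end early on stable resolution, "which is defined as 2 consecutive months’ responses of ‘completely recovered’ or ‘much better". It adds: "After stable resolution, data collection for the primary outcome via text message ceases". The footnote to Table 1 repeats the rule: "defined as 2 consecutive months’ responses of ‘completely recovered’ or ‘much better".
- **Sensitivity analyses (of the primary endpoint)**: under secondary definitions of good outcome, "we will use three separate secondary classifications based on ‘stable resolution" and two related terms. Here stable resolution is "two consecutive recordings of ‘completely recovered’ or ‘much better". Stable improvement is built the same way, with 'better' also counting as positive. No minimum time between the two replies is given.
- **Schedule** (Primary outcome section): "Data collection for the primary outcome occurs weekly" for the first 4 months in all participants; after that, "the text message data collection changes to once every 4 weeks". The sensitivity section places the switch in time: "especially after the first 16 weeks when outcome data is collected monthly".

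The primary endpoint is the first single positive reply and requires no persistence.

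**The concern.** One term carries two rules that coincide only in the 4-weekly phase. In the weekly phase, two replies 7 days apart satisfy the analysis rule but not the monthly one. Someone who resolves in week 3 is called stable after a week. Someone who resolves at week 24 is called stable only if still positive at week 28.

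The primary endpoint counts a single positive reply, so these two-reply classifications are the only listed time-to-event checks that ask whether resolution was sustained. The test is shortest in the first 16 weeks, the period in which most treatment is expected to be completed (Table 1 footnote). The article handles the schedule change for the timing of the event, through interval-censoring methods, but not for the persistence required. A reader of the results would also be likely to give 'stable resolution' the monthly meaning stated twice elsewhere in the article.

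**Working it through.** The plan states no event rate or effect size for these classifications, so there is no figure of its own to reproduce. The rules can be set side by side and their effect gauged under stated assumptions. **All resolution and relapse rates below are assumptions.**

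**1. Persistence required by two consecutive recordings.** Up to week 16 the gap is 1 week. From then on (16 to 20, 20 to 24, and so on) it is 4 weeks, a fourfold change. With weekly relapse probability r, the chance of staying resolved throughout the gap is 1 − r early and (1 − r)⁴ late:

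| r | early | late |
|---|---|---|
| 5% | 0.95 | 0.81 |
| 10% | 0.90 | 0.66 |
| 20% | 0.80 | 0.41 |

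The late rule sees only the two ends, so an unseen lapse and recovery still passes. With an assumed weekly chance h = 3% of resolving and π = h/(h + r), the chance of being positive at the second end is π + (1 − π)(1 − h − r)⁴ = 0.82, 0.67 and 0.44. The contrast with the early rule remains.

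**2. Share called stable by week 16 in a single arm.** Two-state weekly course with a 4% weekly chance of resolving. The 4-week rule requires every reply over a 4-week span to be positive.

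| Weekly relapse | two recordings | 4-week rule |
|---|---|---|
| 0% | 46% | 39% |
| 5% | 44% | 32% |
| 10% | 42% | 27% |
| 20% | 38% | 17% |

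The zero-relapse row follows directly. Two recordings need a first positive by week 15: 1 − 0.96¹⁵ = 0.458. The 4-week rule needs one by week 12: 1 − 0.96¹² = 0.387. With permanent resolution nobody is falsely stable, so that 7-point gap is only later confirmation. Part of the gap in the other rows has the same cause and must not be read as false stability.

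**3. Effect on the between-arm comparison.** Simulated two-state course, 20,000 per arm, recorded at weeks 1 to 16 and then 20, 24, … 52. Cox hazard ratio (HR) under two recordings against the 4-week rule. The weekly resolving chance is 3% in both arms unless stated.

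| Scenario | Weekly relapse | two recordings | 4-week rule |
|---|---|---|---|
| No arm difference | 0–30% | 0.98–1.01 | 0.97–1.01 |
| Proportional hazards, 4.35% v 3% | 0–30% | 1.44–1.45 | 1.43–1.48 |
| 5% v 3% in weeks 1–16 only | 0% | 1.36 | 1.36 |
| same | 5% | 1.37 | 1.32 |
| same | 10% | 1.42 | 1.33 |
| same | 20% | 1.46 | 1.27 |
| Hazards cross at week 16 (5% then 2%, v 2% then 5%) | 0% | 1.05 | 1.05 |
| same | 10% | 1.16 | 0.94 |

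The departures from 1 in the first row are simulation noise.

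**4. Lower relapse.** The Background cites recovery after one year of 49–58%. In a two-state model with a 4% weekly chance of resolving, the long-run resolved share is 0.04/(0.04 + r). Relapse of 5, 10 and 20% gives 44, 29 and 17%, all below that range; relapse of about 3–4% falls within it. At 3% and 4% relapse, with 5.8% v 4% weekly resolving, the HRs are 1.46 v 1.44 and 1.44 v 1.43 under proportional hazards. With the advantage confined to weeks 1–16 they are 1.27 v 1.24 and 1.27 v 1.23.

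**The case against.** A reader might infer that the analysis rule favours whichever arm improves earlier. The documents do not support that. Both arms share one schedule, and an arm with a uniformly higher resolution rate also improves earlier yet gains nothing consistent. A shift needs relapse together with an arm difference concentrated before week 16, or hazards that cross. The article makes such a pattern conceivable: its Background describes short-term relief from injections and faster recovery after surgery with similar later outcomes, fast-track assessment is due within 4 weeks, and Assumption checking provides for non-proportional hazards. It supplies no relapse rate and no evidence that the pattern will occur.

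The other objections stand in part:

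- These are secondary classifications within the sensitivity analyses, so the primary result does not depend on them. That limits the consequence but does not remove the contradiction.
- The monthly wording is a rule for stopping texts in months 4 to 12. Anyone stopped under it already meets the two-recordings rule, so no event is lost. True, but the same name is still given to a different quantity.
- Global perceived change at 4 and 12 months also bears on durability. It gives two fixed points, not a check on a time-to-event result.
- Requiring every weekly reply over 4 weeks would make the early test harder if missing texts counted as failure. At the cited 83% response rate, and assuming independent replies, five in a row are complete 0.83⁵ = 39% of the time and two in a row 0.83² = 69%. This is right, and the fix must allow for it.

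**Conclusion.** The contradiction is on the page and does not depend on any assumption: two definitions of one term, and an analysis version whose persistence requirement rises from 1 to 4 weeks at week 16. Stable improvement has the same change. It should be corrected because it alters what these analyses measure and how their label will be read.

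The consequence for the arm comparison is conditional. There is no bias under the null or without relapse, and none of material size under proportional hazards. With relapse and a benefit concentrated before week 16, the HR can shift towards that arm: by about 0.03–0.04 at 3–4% weekly relapse, by 0.09 (1.42 v 1.33) at 10%, and by more if hazards cross. These sizes rest on a simple two-state model with assumed rates. The week-16 percentages overstate the problem if read alone, because part of each gap is later confirmation.

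**What to change.** Use one definition in the Primary outcome section, the Table 1 footnote and the sensitivity analyses, with the same minimum span in both phases. For example: positive replies at least 4 weeks apart with no observed non-resolved reply between them. A missing intermediate text should not count as failure, so that early resolvers do not face a harder test. Two consecutive positive 4-weekly replies already satisfy this in the later phase. Apply the same span to stable improvement, reading the intermediate condition as no observed reply short of 'better'. State whether the event is dated at the first or the confirming reply. The two-recordings version may be kept under a different name.

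The cost is a few sentences. Weekly replies are already collected from everyone for 4 months, so no new data are needed. The downside is fewer and later-confirmed stable events before week 16. One small asymmetry remains, since brief lapses can be seen in weekly data and missed in 4-weekly data.
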